#### Data Analysis Plan for Aim 1: Examining the Prediction Accuracy of the Within-Group Models Using the Random Forest Algorithm

The first research question asks: how well can one predict program completion and anticipated gains within (1) the full-coach condition, (2) the automated coach condition, and (3) the contingent coach condition? To ensure that the different programs do not account for a substantial portion of the variance when predicting program completion or changes in relationship satisfaction, a test will be performed where 2 models will be created and compared. In the first model, all predictors will be interacted with the level of coaching (full, contingent, and automated) and the program assignment (ie, OurRelationship and ePREP) resulting in Predictor×Treatment×Coaching interactions. However, the second model will maintain all predictors by coaching interactions but drop all program assignment interactions (ie, resulting in only Predictor×Coaching interactions). Next, the root mean square error (RMSE) between the 2 models will be compared. If the null hypothesis does not get rejected (H_0_: RMSE_Model 1_ = RMSE_Model 2_), program assignment will be ignored resulting in 3 conditions (full, contingent, and automated coaching), which will be used in the proceeding aims. If the interactions account for a significant portion of the variance (H_a_ = RMSE_Model 1_ ≠ RMSE_Model 2_), independent models will be built by treatment (ie, OurRelationship or ePREP) and coach condition (full, automated, and contingent) resulting in 6 models: OurRelationship full coach, OurRelationship automated coach, OurRelationship contingent coach, ePREP full coach, ePREP automated coach, and ePREP contingent coach, which will be used in the proceeding aims.

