## Results

Data collection was completed in October 2020 and data are being prepared to be analyzed. Overall, 63.8% (286/448) of individuals completed the material in the OurRelationship coach condition, 53.8% (155/288) of couples completed the OurRelationship contingent coach condition, and 54.5% (157/288) of individuals completed the OurRelationship automated (ie, email only) condition. Similarly, 69.4% (306/441) of couples completed the content in the ePREP coach condition, 74.2% (210/283) completed the content in the ePREP contingent coach condition, and 66.2% (188/284) of couples completed content in the ePREP automated (ie, email only) condition. Currently, no other outcomes except for completion rates have been analyzed. Given the large sample size within and between conditions, the current sample is large enough to identify potential predictor variables and evaluate their prediction accuracy. This study is expected to conclude in the summer of 2022.

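### If the Aim 1 RMSE test is not rejected, program is dropped from every pooled model, although completion already differs by 11.4 points between the two programs

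*Protocol article*

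**What the plan says.** The section on Aim 1 compares two models. The first interacts every predictor with coaching level and program. The second is to "drop all program assignment interactions (ie, resulting in only Predictor×Coaching interactions"). The stated purpose is "To ensure that the different programs do not account for a substantial portion of the variance when predicting program completion" or satisfaction change. If equality of RMSE is not rejected, "program assignment will be ignored resulting in 3 conditions (full, contingent, and automated coaching), which will be used in the proceeding aims". If it is rejected, six separate program-by-coaching models are built. So program either defines separate models or is absent. It is also not among the candidates listed under Measures: Predictor Variables.

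The sections on Aims 2 and 3 restate the trigger differently. Aim 2 builds program-specific models if the interactions give a lower RMSE, better sensitivity or better specificity. Aim 3 does so for a better RMSE. Neither mentions rejecting a null hypothesis.

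The Results section already reports completion by program and coaching level, for example "53.8% (155/288) of couples completed the OurRelationship contingent coach condition" and "74.2% (210/283) completed the content in the ePREP contingent coach condition".

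**The concern.** The two models are defined by their program interactions, but the action on non-rejection removes program entirely, main effect included. Not detecting an interaction is no reason to delete a main effect. Because program was randomized, baseline characteristics cannot stand in for it, and the pooled forests would give a couple the same completion probability in either program.

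Completion is the first outcome in the plan, and the abstract's objective includes assigning couples to programs as well as to coaching levels. A model without program cannot inform the first of those choices. If its completion predictions are also biased in a known direction for each program, sensitivity, specificity and predictive values suffer as well.

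**Working it through.** **Inputs.** Completion counts from the Results section. They are counts of individuals (for example 2×226 − 4 = 448), although some are labelled couples. All six printed percentages reproduce.

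| Coaching | OurRelationship | ePREP | ePREP minus OurRelationship |
|---|---|---|---|
| Full | 286/448 = 63.8% | 306/441 = 69.4% | 5.5 points |
| Contingent | 155/288 = 53.8% | 210/283 = 74.2% | 20.4 points |
| Automated | 157/288 = 54.5% | 188/284 = 66.2% | 11.7 points |

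**Step 1. Overall program difference.** OurRelationship: (286+155+157)/(448+288+288) = 598/1024 = 58.4%. ePREP: (306+210+188)/(441+283+284) = 704/1008 = 69.8%. Difference: 11.4 points.

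SE = √[0.584×0.416/1024 + 0.698×0.302/1008] = 0.0211, giving a 95% CI of 7.3 to 15.6. Doubling the variance, as if partners always agreed (an assumption), gives SE = 0.0299, z = 3.83 and a 95% CI of 5.6 to 17.3.

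**Step 2. Average error if program is ignored.** Pooled rate = sum of completers / sum of individuals at that coaching level. Error = pooled rate minus the program's own rate.

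| Coaching | Pooled | Error, OurRelationship | Error, ePREP |
|---|---|---|---|
| Full | 592/889 = 66.6% | +2.8 | −2.8 |
| Contingent | 365/571 = 63.9% | +10.1 | −10.3 |
| Automated | 345/572 = 60.3% | +5.8 | −5.9 |

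The ePREP contingent and automated denominators (283, 284) are the reverse of what the removals under Participants imply (2×143 − 2 = 284 and 2×143 − 3 = 283), so those two rows may be interchanged. If they are, the contingent errors become about 6 points and the automated errors about 10. The overall program difference is unchanged.

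**Step 3. What RMSE registers.** For a 0/1 outcome predicted by its cell rate, RMSE = √(mean of p(1−p)). With pooled rates this is √0.2295 = 0.479. With program-specific rates it is √0.2253 = 0.475. The ratio is 0.99.

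**Step 4. Chance of rejection.** Assumptions, none of them in the article: Model 2 holds no program term, the printed cell rates are the known truth and apply to couples, there are no other predictors, and the test is a two-sided 5% paired test on squared errors.

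| Share of couples in test set | Test rejects |
|---|---|
| 20% | about 17% |
| 30% | about 22% |
| 50% | about 35% |
| All 1024 | about 60% |

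If Model 2 instead keeps a program main effect, both models contain it and the comparison cannot see it at all.

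**Step 5. The Aim 3 contrast, full minus contingent.** Pooled: 66.6 − 63.9 = +2.7 points. OurRelationship: 63.8 − 53.8 = +10.0. ePREP: 69.4 − 74.2 = −4.8, 95% CI −14.2 to +4.6 with doubled variance. With the two ePREP rows interchanged, ePREP becomes 69.4 − 66.2 = +3.2.

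**The case against.** **The later sections may prevent the loss.** Under the Aim 2 and Aim 3 wording, any better RMSE leads to program-specific models. On the assumptions of Step 4, RMSE is lower with program in about 88% of draws on a 30% test set and 99% on all couples, although fitted forests would do worse than known rates. This stands. A reader might infer that program will be discarded as a matter of course; the document does not support that, because the harm depends on the Aim 1 rule being the one applied. But the conflict does not repair the Aim 1 rule. It leaves the operative rule unsettled.

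**The test may cover the main effect.** If Model 2 has no program term, as its description and the stated purpose suggest, the comparison does include the main effect. This stands too, and is why Step 4 assumes it. Even so, the test is weak.

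**Ten points is the worst cell.** Correct. In full coaching, the largest group, the error is under 3 points and the program difference is not clear (95% CI −0.6 to 11.7 on individuals). The Introduction also reports equal adherence in an earlier comparison of the programs with four calls, so it was reasonable to consider pooling.

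**Opposite coaching effects.** A reader might infer from Step 5 that contingent coaching beats full coaching in ePREP and that pooling hides a reversal. That is not established: the interval includes zero and the sign depends on rows that may be interchanged. Moreover, a program effect that is additive on the probability scale cancels in this contrast. Only program-by-coaching differences can distort it.

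Nothing here shows harm to the second outcome, gain in relationship satisfaction.

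**Conclusion.** The point holds, conditionally. The Aim 1 section states a rule that removes a randomized factor from all pooled models on the strength of a non-rejected RMSE comparison, when the article's own data already show that factor to be associated with completion (11.4 points, 95% CI 5.6 to 17.3 with doubled variance). If the rule is applied and the test is not rejected, average completion predictions by program are off by about 3, 6 and 10 points for full, automated and contingent coaching, the last two exchanging if the ePREP rows are interchanged. Non-rejection is likely on a test set of up to half the couples and far from excluded on all of them.

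The size rests on the printed counts of individuals standing in for completion by couple. The rejection figures rest on an assumed split and an assumed form of test. This is a should-fix: the bias is known and avoidable, but it is confined to one branch and one outcome, and is small in full coaching.

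**What to change.** In the Aim 1 section, replace the instruction to ignore program with wording such as: *program is kept as a candidate predictor in each coaching-level forest and as a term in the Aim 2 and Aim 3 regressions, and predictions and contrasts are computed at a stated program.* Use the Aim 1 comparison only to decide whether fully separate forests per program are needed. Say whether Model 2 contains a program main effect. Bring the triggers in the Aim 2 and Aim 3 sections into line with that single rule.

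The cost is one binary column and a few sentences. At the time of the article the data were still being prepared and only completion rates had been analysed, so the change was then still open.

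One caution: a single added column may recover only part of the program difference. In one illustrative forest (286 contingent couples, 20 noise predictors, 5 variables tried per split, all assumed) it recovered about 45% of the gap. Predicted and observed completion should therefore be compared by program within each coaching level, and separate forests or a forced program term considered if they disagree.

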**Figure 1 figure1:**
[figure not shown]
A two-by-two table visually displaying model characteristics.

#### Data Analysis Plan for Aim 2: What Are the Most Important Within-Group Predictors?

The second research question is: what are the most powerful predictors of treatment adherence and gains in relationship satisfaction within (1) the full-coach condition, (2) the automated coach condition, and (3) the contingent coach condition? If, in aim 1, the interaction terms result in a lower RMSE, better sensitivity, or better specificity, models will be constructed based on treatment assignment (ie, OurRelationship or ePREP) and coach assignment (ie, full, contingent, or automated). One statistically powerful way to test the most potent predictors of treatment adherence and gains is through the use of variable importance (VIMP). VIMP is a nonparametric approach within the random forest algorithm, which can help investigators identify which variables play a key role in predicting a binary (eg, program completion) or continuous (eg, improvements in relationship satisfaction) variable [53]. VIMP has been calculated in many ways in the past; however, one way that has shown promise has been through permutation (ie, Briemen–Cutler) importance [53]. This method randomly changes a given variable’s out-of-bag data and compares and averages the permuted prediction error with the original error resulting in VIMP [53]. This process not only helps identify which variables play a key role in prediction but also overcomes issues of overtesting using bootstrapping. Recent studies have used these out-of-bag estimates to generate CIs to test whether a variable has a meaningful effect in predicting an outcome with great success [53]. Indeed, these studies have suggested that 95% CIs that do not include zero will be assumed to have reliable predictors [53]. After identifying the most powerful predictors using VIMP, a multiple regression model will be estimated using the reduced set of variables to aid in the interpretation of the main effects, helping clinicians identify predictors of treatment adherence and gains.

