These models will be built using the random forest algorithm [52]. The random forest algorithm reduces overfitting by bootstrapping or fitting several different trees to subsets of the sample to inform the predictions (ie, bagging) [52]. Once the ensemble of trees is generated, the outputs from all the trees are aggregated, and the prediction is generated. Its ability to predict treatment outcomes for individuals and couples has been proven in several precision medicine studies [13,14]. Thus, in the first aim of this study, the random forest algorithm will be used to accurately predict the within-group likelihood that a couple completes the OurRelationship and ePREP programs in (1) the full-coach condition, (2) the automated coaching condition, and (3) the contingent coach condition as well as the magnitude of their gains in relationship satisfaction. The model characteristics address the model performance on the test data set*.* For binary outcomes (program completion), the model characteristics used to evaluate the validity of the model include sensitivity, specificity, positive predictive value, and negative predictive value of the model built on the test data set (Figure 1). Model sensitivity is measured by the percentage of true positives (ie, a/a+c). Model specificity is the percentage of true negatives (ie, d/d+b). A model’s positive predictive value yields a positive test result and the probability that the participant will complete the program (ie, a/a+b). Finally, a model’s negative predictive value yields negative test results and the probability that the participant will not complete the program (ie, d/d+c). Good models for binary outcomes include models whose sensitivity, specificity, positive predictive value, and negative predictive value are closest to 1. For continuous outcomes (ie, improvements in relationship satisfaction), model accuracy will be evaluated using the RMSE. The RMSE is a measure of absolute fit and is the square root of the variance of the residuals; smaller values indicate better fit.

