#### Data Analysis Plan for Aim 3: Predicting Between-Group Treatment Outcomes

Assuming that the models from the previous aim have levels of prediction accuracy, each of the within-group models will be used to generate predicted outcomes for each couple’s likelihood of adhering to the program as well as their treatment gains, creating counterfactual estimates of program completion and treatment gains as if each couple in the data set completed each intensity and method of coach contact [14].

To do this, the within-group models built in aim 1 will be used to generate potential outcomes for each couple’s likelihood of adhering as well as their gains in a (1) full coaching, (2) automated coaching, and (3) contingent coach conditions. If, in aim 1, the interaction terms result in a better RMSE, models will be constructed based on treatment assignment (ie, OurRelationship or ePREP) and coach assignment (ie, full, contingent, or automated). The estimates between the conditions for each couple’s between-group treatment differences between the full and automated coaching conditions can be understood as:

where 
[figure not shown]
 is the between-group likelihood of treatment adherence or gains for couple x, *Ŷ*(*x, Full Coach*) is the within-group likelihood of treatment adherence or gains for couple x in the full-coach condition, and *Ŷ*(*x, Contingent Coach*) is the within-group likelihood of treatment adherence or gains for couple x in the contingent coach condition [14]. These hypothetical between-group outcomes will then serve as dependent variables in a second random forest to calculate VIMP, which will identify the most powerful predictors of between-group differences. After identifying the most powerful predictors using VIMP, a multiple regression model will be estimated using the reduced set of variables to aid in the interpretation of the main effects. This process will thereby help clinicians determine which couples should be assigned to which level of coach contact.

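### Aims 1, 2 and 3 give three non-equivalent criteria for splitting the models by program, and the Aim 2 criterion is too lax for completion

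*Protocol article*

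**What the plan says.** The Aim 1 plan compares two models by RMSE: one with predictor-by-program-by-coaching interactions, and one with predictor-by-coaching interactions only. The pooling branch reads "If the null hypothesis does not get rejected (H_0_: RMSE_Model 1_ = RMSE_Model 2", and then "program assignment will be ignored resulting in 3 conditions (full, contingent, and automated coaching), which will be used in the proceeding aims". The splitting branch begins "If the interactions account for a significant portion of the variance (H_a_ = RMSE_Model 1_ ≠ RMSE_Model 2" and leads to separate models by program and "coach condition (full, automated, and contingent) resulting in 6 models". Neither the test nor its significance level is named.

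The Aim 2 plan restates the splitting condition: if "the interaction terms result in a lower RMSE, better sensitivity, or better specificity, models will be constructed based on treatment assignment". The Aim 3 plan states it again: "If, in aim 1, the interaction terms result in a better RMSE, models will be constructed based on treatment assignment". Aim 3 also says that its predictions come from the models built in Aim 1.

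On metrics, the Aim 1 plan says: "For continuous outcomes (ie, improvements in relationship satisfaction), model accuracy will be evaluated using the RMSE". For completion it lists sensitivity, specificity and the two predictive values.

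**The concern.** The three conditions differ in metric, in whether a test is needed, and in direction. The choice matters because every variable-importance result and every counterfactual prediction comes from the chosen model set. If Aim 2 interpreted six models while Aims 1 and 3 used three, the accuracy reported in Aim 1 would not describe the models whose predictors are interpreted. A split also roughly halves the couples behind each model. The Results section reports completion rates by arm, so three available rules leave a choice open after one outcome has been seen.

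**Working it through.** **Counts.** From the Participants section, the arms are 226, 145 and 145 (OurRelationship), 222, 143 and 143 (ePREP) and 224 (waitlist). They sum to 1248, as stated, with 1024 in the treated arms. Two programs times three coaching levels gives the stated 6 models. Pooled, the cells are 226 + 222 = 448 (full), 145 + 143 = 288 (contingent) and 145 + 143 = 288 (automated). Split, they range from 143 to 226.

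**The three rules on the same Aim 1 result.** Model 1 has the program interactions and Model 2 does not. Entries are the number of models called for.

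| Model 1 against Model 2 | Aim 1 | Aim 2 | Aim 3 |
|---|---|---|---|
| RMSE significantly lower | 6 | 6 | 6 |
| RMSE lower, not significant | 3 | 6 | 6 |
| RMSE higher, not significant; sensitivity or specificity slightly better | 3 | 6 | 3 |
| RMSE significantly higher; sensitivity and specificity no better | 6 (from the ≠) | 3 | 3 |

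Only the first row gives the same answer throughout.

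**How often the Aim 2 trigger fires for completion when program is irrelevant.** Take two equivalent models and ignore ties, so that each metric is better with probability 0.5.

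- Independent metrics: 1 − 0.5 × 0.5 = 75%.
- Correlated metrics: 1 − [1/4 + arcsin(ρ)/(2π)]. At ρ = +0.5 this is 1 − (1/4 + 1/12) = 67%. At ρ = −0.5 it is 1 − (1/4 − 1/12) = 83%.

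**Simulation.** Random forests were fitted with no program effect and the documented arm sizes, 200 replicates per scenario. The document does not give the remaining settings, so these were assumed: 17 predictors, 30% test set, 200 trees, cut-off 0.5. The test column is a paired comparison of squared errors at 5%, two-sided.

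| Predictor signal | Sensitivity better | Specificity better | Either | Both | Squared error lower | Paired test rejects |
|---|---|---|---|---|---|---|
| None | 25.5% | 55% | 68% | 12.5% | 38.5% | 7% |
| Moderate | 43% | 39% | 67.5% | 14.5% | 38% | 8.5% |
| Stronger | 46% | 32% | 62% | 16% | 32% | 11.5% |

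The Monte Carlo standard error of the Either column is about √(0.65 × 0.35/200) = 3.4 points. Two smaller sets used separate forests per cell. One of 51 runs gave 55% for either metric (95% interval about 41-69%). One of 60 runs gave 72% for the full three-metric rule (about 61-83%) and 3% for the paired test.

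**Metric for completion.** Set beside the Aim 1 statement that ties RMSE to satisfaction, the Aim 1 and Aim 3 splitting rules name nothing specific to completion. Only Aim 2 does.

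**The case against.** The strongest reply is that there is only one decision. Aim 1 says its result is carried forward, the conditions in Aims 2 and 3 both point back to Aim 1, and Aim 3 reuses the Aim 1 models. On that reading the later sections are loose reminders. This is possible, and it means the aims need not end up on different model sets. It does not remove the conflict, because Aim 2 brings in sensitivity and specificity, which the Aim 1 rule never mentions, and nothing says which wording governs.

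A second reply is that Aim 2 can be read respectively: RMSE for satisfaction, the other two metrics for completion. For satisfaction the Aim 2 and Aim 3 rules then coincide, leaving two rules rather than three. The either-metric trigger for completion remains.

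A third reply is that the sentence containing the ≠ also requires the interactions to account for significant variance, so a worse model was probably not meant to trigger a split. That is likely the intention, but the stated hypothesis does not say so.

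Two stronger readings should be resisted. A reader might infer that any program split found here would be a chance result. The documents do not support that: completion is higher for ePREP at every coaching level (69.4% against 63.8% full, 74.2% against 53.8% contingent, 66.2% against 54.5% automated; pooled 704/1008 = 69.8% against 598/1024 = 58.4%), so a real program difference is possible. A reader might also infer that sensitivity and specificity trade off so that one nearly always improves. The simulation does not show it: under moderate signal, independence predicts 0.43 × 0.39 = 16.8% for both better, and 14.5% was seen. The lax trigger comes from needing only one of two untested gains.

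**Conclusion.** The point holds on the text alone: the three criteria are not equivalent, and the same Aim 1 result can call for 3 models in one section and 6 in another. For completion, the Aim 2 trigger would split in roughly 60-75% of samples with no program effect, against about 3-12% for a paired 5% test. Those ranges rest on assumed test fraction, cut-off, predictors and forest settings; they show the order of the problem, not a precise rate. The two-sided alternative and the missing completion criterion in Aims 1 and 3 are further defects of the same rule. Because the Procedure section says the analyses will be preregistered, one rule should be fixed there before the models are fitted.

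**What to change.** Make the pool-or-split decision once per outcome, in Aim 1, and state three things:

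- **Metric.** For example, RMSE for satisfaction and the Brier score for completion. The Brier score is the mean squared error of the predicted probability, so it stays close to the existing RMSE idea while making clear what is computed.
- **Decision rule.** Either a one-directional test at a stated alpha or a stated margin.
- **Direction.** Split only if the program-interaction model predicts better.

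In Aims 2 and 3, replace the separate conditions with a sentence such as: *the model set selected in Aim 1 for that outcome is used*. Drop the sensitivity-or-specificity trigger; both can still be reported as performance measures. The cost is a few sentences in the plan and the preregistration, with no new data.

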### This Study: Research Aims and Hypotheses

Given past research, this study has 3 aims. The first aim is to investigate how well we can predict the completion rates and changes in relationship satisfaction. As model evaluation has rarely been used in this area of research, no specific hypotheses have been posited. The second aim of this study is to document the most powerful predictors of treatment adherence and gains in relationship satisfaction within 3 different levels of coaching. More specifically, what are the most powerful predictors of treatment adherence and gains in relationship satisfaction in a full-coach condition (with 4 scheduled 15-minute phone calls), automated coach condition (where couples only receive emails), and a contingent coach condition (where couples only receive scheduled coach calls after displaying a pattern of nonadherence)? Although many of the findings in this area of research are inconclusive, 2 findings are relatively consistent: lower external stress and higher intrinsic motivation both predict treatment adherence and gains. Thus, we hypothesize that, regardless of coach assignment, lower external stress and higher intrinsic motivation will emerge as reliable predictors of better adherence to the web-based program and subsequent treatment gains. In the final aim of the study, we intend to use the information gathered in the first 2 steps to determine the most powerful predictors of between-group differences. More specifically, what baseline characteristics are indicative of a given couple’s adherence or gains in relationship satisfaction to couples assigned to the full-coach program compared with automated coaching, contingent coaching, or the waitlist control condition? As this area of research is relatively underdeveloped, no specific hypotheses will be posited.

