##### Psychological Distress

To assess individual distress, this study intends to use the Kessler Psychological Distress Scale (*During the past 30 days, how often have you felt nervous*) [47]. This is a high-precision, 6-item, Likert-style measure developed using the item response theory. In a past RCT with a low-income sample, this scale had good internal consistency (Cronbach α=.86) [48]. Furthermore, this scale has excellent discrimination when attempting to detect severe cases of psychopathology, providing evidence of its validity [47].

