##### Perceived Stress

To assess perceived distress, this study intends to use the Perceived Stress Scale, a 4-item Likert-style measure (*In the last 30 days, how often have you felt that you were unable to control the important things in your life?*) [49]. A past RCT has indicated that internal consistency was acceptable (Cronbach α=.74) [48].

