##### Chaos

Another measure of external stress will include a single-item measure of chaotic events that an individual may experience in their relationship. This will be assessed using a check-all-that-apply item developed by the ACF; that is, *the following are a list of events that may cause stress for you and your partner. Check each thing (or similar thing) that has happened to you in the past month*. Some of the answers from this item include *changes in work schedule, changes in childcare, changes in family structure, or changes in finances*.

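### The stress and motivation hypothesis concerns two constructs, but the plan judges it one questionnaire at a time and gives no rule for combining the results

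*Protocol article*

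**What the plan says.** The section on research aims and hypotheses in the Protocol article states one substantive hypothesis: whatever the coach assignment, "lower external stress and higher intrinsic motivation will emerge as reliable predictors of better adherence to the web-based program and subsequent treatment gains". Aims 1 and 3 carry none.

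In the Measures section, external stress is four separate predictors: psychological distress ("this study intends to use the Kessler Psychological Distress Scale"), perceived stress ("this study intends to use the Perceived Stress Scale, a 4-item Likert-style measure"), chaos ("Another measure of external stress will include a single-item measure of chaotic events") and a single general health item. Motivation is two: grit and motivation to change. The averaging described at the start of Data Analysis is across the two partners, not across measures.

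The Aim 2 analysis plan fixes both the unit and the rule. The unit is the single variable: "This method randomly changes a given variable"'s "out-of-bag data and compares and averages the permuted prediction error with the original error resulting in VIMP". The rule is that "95% CIs that do not include zero will be assumed to have reliable predictors". The same paragraph says the bootstrapping in this process overcomes overtesting. A multiple regression follows, but only on the variables that importance has selected, and only to help interpret main effects. No joint importance, composite score or combining rule is stated.

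**The concern.** The hypothesis is about constructs and the decision rule is about single columns, so the plan does not say which pattern of results would confirm it. With four stress measures, three coaching levels and two outcomes there are 4 × 3 × 2 = 24 stress verdicts, or 48 if Aim 1 leads to separate models by program.

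Correlated measures make this matter in two ways. When one is permuted, the forest still has the others, so each can look unimportant although the set matters. A measure with no effect of its own can also gain importance as a stand-in for something it correlates with, such as baseline relationship satisfaction. Judged measure by measure, the verdict on stress is then insensitive; judged by whether any measure passes, it is too permissive. The study's one stated hypothesis could be confirmed or rejected according to a reading chosen after the results are known.

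**Working it through.** The article gives no power figure and no correlation among measures, so there is nothing of its own to reproduce. The question was examined by simulation.

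**Inputs from the article.** Couples pooled over programs: full coach 226 + 222 = 448; contingent and automated 145 + 143 = 288 each. Predictors: 6 demographic + 7 relationship + 4 stress + 2 motivation = 19. Decision rule: 95% interval excludes zero.

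**Assumptions.** A measure, or the jointly permuted block, is flagged when VIMP − 1.96 × SD > 0, where SD is the Monte Carlo SD of its VIMP.
- Setting A: regression forests, 100 data sets per scenario; distress and perceived stress correlate 0.65, other stress pairs 0.3, and distress and perceived stress correlate 0.4 with the relationship measures.
- Setting B: a separate run with the same assumed correlations, 100 data sets per scenario.
- Setting C: 200 data sets per scenario, stress measures equally correlated at r, all other predictors independent noise, stress explaining 6% or 12% of the outcome (latent scale if binary).
- Setting D: as A, with relationship measures correlating 0.5 with each other and 0.15 with chaos and health.

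**Stress truly matters, effect shared by the four measures**

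| Setting | n | Each measure | Any of four | Joint |
|---|---|---|---|---|
| A, 0.25 SD | 448 | 24, 29, 11, 12% | 56% | 62% |
| A, 0.25 SD | 288 | 15, 19, 14, 8% | 45% | 39% |
| B, 0.25 SD | 448 | 9-22% | 46% | 46% |
| C, binary, 6%, r=0.6 | 448 | 12-16% | 47% | 40% |
| C, binary, 12%, r=0.6 | 448 | 12-28% | 63% | 69% |
| C, continuous, 6%, r=0.6 | 448 | 13-20% | 49% | 54% |
| C, binary, 6%, r=0.6 | 288 | 8-14% | 35% | 23% |
| C, binary, 6%, r=0.3 | 448 | 10-14% | 42% | 36% |

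Each measure alone is flagged well below the joint rate in every row. Any of four is close to, or above, the joint rate.

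**Stress has no effect of its own**

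| Setting | n | Any of four | Joint |
|---|---|---|---|
| B, no effects at all | 448 | 20% | 2% |
| A, only satisfaction matters (0.4 SD) | 448 | 34% | 12% |
| B, only satisfaction matters | 448 | 31% | 12% |
| D, only satisfaction matters | 448 | 23% | 9% |
| D, only satisfaction matters | 288 | 19% | 6% |

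In setting C a pure noise variable is flagged about 3.7% of the time, so four independent ones give 1 − (1 − 0.037)^4 = 14%. Even at the nominal one-sided 2.5%, 1 − 0.975^4 = 9.6%. In the satisfaction-only scenario of setting A, the four measures are flagged singly in 16, 11, 7 and 6%.

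**Spillover inside the stress set** (setting C, n=448, only one measure active). The three inactive measures are flagged in 7-14% at r=0.6, against 3.3-5.5% for noise. At r=0.3 the figure is 4-5%, close to noise.

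Monte Carlo error is about 5 points for a rate near 46% in 100 data sets (√(0.46 × 0.54/100) = 0.050) and 2 to 3.5 points in setting C.

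**The case against.** The strongest reply is that nothing need be missed or spurious. At least one stress measure is flagged about as often as the joint test succeeds, so a reader who infers that a real stress effect will be missed goes further than the documents allow. That depends on a combining rule the article does not give. Much of the low power comes from modest effects and sample size; the joint test at 0.25 SD itself fails in 38-61% of setting A data sets. This stands.

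A reader might also infer that a stress scale with no effect of its own will wrongly be called reliable. The article asks about prediction and makes no claim of a contribution beyond satisfaction. A proxy that improves prediction is a legitimate predictor, and flagging it is an error only if it is read as that measure's own effect. This stands too, and the spillover is modest and rests on correlations the article does not report.

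The follow-up regression helps more than it may seem. If regression significance were also required, false positives fall to about 8-11% in setting B; in setting D, with 448 couples, they fall from 23% to 9%. But the article gives the regression an interpretive role and no threshold, and it cannot restore a measure already screened out.

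Finally, how results combine could be detail for the preregistration. Had the article been silent on testing, that would be enough. It is not: it fixes the unit and the rule, and the unit does not match the hypothesis.

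**Conclusion.** The mismatch is in the text and does not depend on simulation: a hypothesis on two constructs is decided by single-variable importance, with no rule for combining results. Its size does depend on assumptions. With correlated stress measures, 448 couples and a 0.25 SD effect, each measure is flagged in about 9-29% of data sets against 46-62% for joint permutation. Any of four matches the joint test's power, but its false-positive rate is about 14-20% with no effects (2% for the joint test in the run that compared them) and 31-34% against 12% when only a correlated satisfaction score matters. Somewhat different assumed correlations give 23% against 9%. The statement that the process overcomes overtesting does not cover this.

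The limits are these. No correlation is documented. The simulated interval uses the Monte Carlo SD, not the out-of-bag interval the plan describes. The 6% and 12% scenarios cover the binary outcome, but motivation was not simulated; with two measures, the argument there is structural. The supported conclusion is that the verdict on the hypothesis is undefined and that both natural readings perform poorly, not that the effect will be missed or falsely found.

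**What to change.** Before the planned preregistration, make the test of the hypothesis one joint permutation VIMP for the four stress measures (same row shuffle for all four) and one for the two motivation measures, for each outcome and coaching level. Call the construct reliable if the lower confidence limit is above zero. For stress this replaces 24 verdicts with 3 × 2 = 6.

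A joint VIMP has no sign. Take direction (lower stress, higher motivation) from the coefficients in a regression that includes all measures of the construct, not only those that passed the screen. Keep single-measure VIMP as the descriptive Aim 2 ranking.

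Permuting within strata of baseline satisfaction should be at most an optional sensitivity analysis. It changes the null to contribution beyond satisfaction and may cost power: in setting D at n=448, 40% against 50% unstratified, with false positives of 5% against 9%.

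The cost is a wording change and one extra permutation per construct on forests already fitted. The small downside is that which individual measure drives a result becomes descriptive. The timing allows it: the Results section says only completion rates have been analyzed so far.
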